#### Primary objectives

To compare histologically confirmed BE diagnosis between intervention and the control arms to determine whether the offer of the Cytosponge™-TFF3 test in primary care results in an increase in BE diagnosis within 12 months of study entry.

#### Secondary objectives

The main secondary objectives are to evaluate the cost and cost-effectiveness of the Cytosponge™-TFF3 test versus usual care. Other secondary objectives include confirming the safety and diagnostic accuracy of the Cytosponge™-TFF3 test and determining the uptake in primary care. Inviting 10% of BEST3 participants for a research endoscopy will enable us to assess the diagnostic accuracy of the Cytosponge™-TFF3 test in primary care. We will also assess the acceptability of the Cytosponge™-TFF3 test to patients, GPs and practice nurses, and their experiences of its use in primary care. Long term objectives are to confirm the prevalence and incidence of BE, EAC and cancer of the gastric cardia in a primary care population consulting with reflux predominant symptoms and to undertake modelling to predict the reduction in EAC related mortality from this strategy.

## Methods

### Design

This is a pragmatic multi-site cluster randomised controlled trial where approximately 120 general practices will be randomised 1:1 to either the intervention or control arm (Fig. 2). Anonymised data will be collected from eligible patients in both arms at baseline and 1 year post entry into the study. Patients will be informed about being entered into BEST3 data collection by letter. Patients in the intervention arm will receive an invitation for a Cytosponge™-TFF3 test in their general practice. Patients with a positive TFF3 test will receive an invitation for an upper gastro-intestinal (GI) endoscopy at their local hospital-based endoscopy clinic to test for BE. In addition to the TFF3-positive patients, 10% of the patients in each arm (who have not had an endoscopy since the start of the trial) will be randomly selected to be invited for an endoscopy at approximately 12 months.

**Fig. 2 Fig2:**
[figure not shown]
BEST3 trial design overview showing both BEST3 anonymous data collection steps (green) and intervention, Cytosponge™-TFF3 test or upper GI endoscopy related procedures (blue)

### Study setting

120 (but up to 150 practices as the project requires) will be recruited from six to seven clinical research networks (CRNs): Eastern, North Thames, North East and North Cumbria, Yorkshire and Humber, but other regions may participate as required. For Information Technology reasons, only practices using Egton Medical Information Systems (EMIS) or TTP’s SystmOne, the two most common systems, will be included in the study.

### Participants

Patients at participating general practices will be selected by GP staff. Inclusion and exclusion criteria for the different stages of BEST3 are outlined in Table 3. In brief, male and female patients aged 50 and over with records of at least 6 months of prescription for acid-suppressant medication (PPI or H2RA) in the last year will be eligible for BEST3 data collection. Patients who also have records of prescriptions for non-steroidal anti-inflammatory drugs (NSAIDs) or an upper GI endoscopy in the previous 5 years will be excluded. These eligibility criteria are based on GP database records, which are not always complete. However, as they are used to increase the power of the trial and not for safety reasons, they only have to be applied based on data as it is available.

**Table 3 Tab3:** Inclusion and Exclusion criteria for the BEST3 trial

Inclusion criteria	Exclusion criteria for		
	BEST3 data collection	Cytosponge procedure	Upper GI endoscopy
• Male and female • Aged ≥50 • Records of ≥6 months of prescription for acid-suppressant medication in the last year	• Recorded regular prescriptions of NSAIDs • Recorded upper GI endoscopy in the previous 5 years as identified from the practice database • Recorded diagnosis of a current or previous oro-pharynx, oesophageal or gastro-oesophageal tumour • Recorded diagnosis of BE • Unable to attend the GP surgery • Deemed not fit enough by their GP, including lacking capacity	• Meeting the guidelines for an urgent endoscopy referral according to NICE guidelines • Recorded diagnosis of an oro-pharynx, oesophageal or gastro-oesophageal tumour (T2 staging and above), or symptoms of dysphagia • Difficulty in swallowing due to a known cerebrovascular accident or neurological disorder • Recorded oesophageal varices, cirrhosis of the liver • Inability to temporarily discontinue anti-thrombotic medication prior to procedure • Having eaten and drank within the preceding 4 h • Received prior surgical intervention to the oesophagus • Known pregnancy • Lacking capacity to provide informed consent	• Upper GI endoscopy during the study period • Severe hypertension (e.g. systolic > 200 diastolic > 100) • Myocardial infarction or any cardiac event within the previous 6 months • Cerebrovascular event or other neurological disorder where swallowing has been affected within the previous 6 months • Any previous treatment such as Photodynamic therapy (PDT) or Radio Frequency Ablation (RFA) to the oesophagus • Anticoagulation therapy/ medication on day of procedure (warfarin, heparin or tinzaparin) according to local guidelines • Other medical condition: low platelets or blood abnormalities that may cause excessive bleeding post procedure • Eaten or drank within the previous 6 h • Preference for sedation and has not brought anyone to accompany them at home. Follow local guidelines • Known pregnancy • Lacking capacity to provide informed consent

#### Number of participants

A minimum of 9000 patients will be entered into the BEST3 trial.

### Randomisation

All patients aged 50 and over who have received at least 6 months’ supply of an acid suppressant drug (either PPI or H2RA) in the last year will be identified by carrying out a database search on coded clinical information. If a practice database search identifies more than 100 eligible patients, 100 patients will be randomly selected to be included in the trial. Once the practice consents to participate in BEST3, each practice will be randomised via block randomisation and stratified by number of eligible patients. Three groups of approximately 40 practices are proposed, each with the following number of patients:Stratum 1 (small practices): 50–60Stratum 2 (medium practices): 61–74Stratum 3 (large practices): 75–100.

The number of patients invited in each stratum and/or the number of strata used might be increased depending on uptake of the Cytosponge. Once a practice has consented to participate in the trial, a database search will be carried out to determine the number of eligible patients and as part of which stratum they will be randomised. Practices will be randomised 1:1 between the intervention and control arms. Randomisation will be balanced by geographical area to ensure that Cytosponge™ clinics will have similar number of bookings in each area. However, as the number of eligible patients in the different practices who will participate is not definite, the number of practices per stratum and the number of strata overall will be adjusted as necessary. The process will be managed so that number of practices in each arm and each stratum will be equal and that the numbers of participants per practice within a stratum will be similar.

### Dates and duration of the trial

Start date: September 2016.

Total duration: 36 months.

### Consent procedures

Patients will be entered into different stages of the trial at different levels of consent.

#### Consent at practice level (opt in)

Firstly, consent will occur at practice level. GPs will provide consent that the practice can be randomised and participants contacted within the BEST3 Trial. GPs will furthermore consent to aggregate anonymised patient data being collated from their practice database and patient notes.

#### Introductory letter provided to patients about use of anonymous data (BEST3 data collection)

All participants across both arms will receive an information letter from their practice outlining that anonymous data collected in the course of their routine care will be included in the study. They will have 14 days to opt out of having their anonymised data collected and analysed as part of BEST3.

#### Written consent for BEST3 intervention and endoscopy (opt in written consent)

Written (individual-level) consent will be obtained before carrying out any procedures. All participants receiving a Cytosponge™–TFF3 test or endoscopy as part of the study will be individually-consented to have this procedure and for the associated clinical data to be collected.

### BEST3 introductory letter and anonymous data collection

#### BEST3 introductory letter

Eligible patients to be included in the study will be sent the introductory letter about the BEST3 data collection from their treating clinician (see above). This letter will additionally explain that they may receive an invitation to participate in later stages of the study.

#### Aggregate data collection for BEST3 trial

Study entry will be defined as 14 days after the date the introductory letter is sent. At this point demographic and medication data will be extracted from the GP database for every patient entered into the study. This dataset will then be aggregated into sex and 10-year age groups (Table 4).

**Table 4 Tab4:** Baseline and follow up data to be collected

Baseline data extract		12 month follow up extract	
Time point/period	Variable	Time point/period	Variable
Baseline	Sex	Baseline	Sex
	Age		Age
	Obesity records	Baseline and 12 months (where available)	Obesity records
	Smoking status		Smoking status
	Alcohol consumption		Alcohol consumption
Previous 12 months	PPI / H2RA prescriptions	Previous 12 months	PPI / H2RA prescriptions
	Other prescription medication: Aspirin, COX2i, antibiotics for *H. pylori* eradication		Other prescription medication: Aspirin, COX2i, antibiotics for H. Pylori eradication
	Heartburn and / or GERD related symptoms		Heartburn and / or GERD related symptoms
			Number of GP and practice nurse visits at home and at the practice
			Number of endoscopy or GI referrals
			Diagnosis of BE
			Diagnosis of EAC or pre-malignant conditions
			Diagnosis of benign oesophageal conditions
			Records on any upper GI specific procedures, e.g. endotherapies or oesophagectomies
			Anonymised endoscopy reports including pathology reports for BE and OC diagnosis; and benign conditions via a tick box (EoE, candida, inflammation, ulcer slough, squamous dysplasia, herpes, other)
			Type of referral: emergency via A&E, 2 week wait / urgent, routine and in or out patient (either form GP records or endoscopy report)
			Number of biopsies (from endoscopy reports)
			Anonymised letters from upper GI consultants

Follow-up data will be collected 12 months after study entry for all patients in each practice, irrespective of study arm and whether they had a Cytosponge™-TFF3 test. Where a new diagnosis of BE or EAC, and / or an endoscopy has been coded in the medical records, data will be extracted from endoscopy and pathology reports and entered into the aggregate data table manually (Table 4). Full baseline data will also be extracted.

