### Economic evaluation

#### Primary endpoint

To gain an in-depth understanding of the health economics of the Cytosponge™-TFF3 test we will undertake a detailed analysis of the cost and cost-effectiveness of the Cytosponge™-TFF3 test versus usual care from the perspective of the NHS and personal social services. For the cost analysis, cost components will include costs of diagnosis using the Cytosponge™-TFF3 test, endoscopies and biopsies, endotherapy, oesophagectomy, and follow-up in primary and secondary care. Volume of resource use data will be collected from practice records up until 12 months after study entry. Unit costs will be taken from published sources such as NHS Reference Costs, the British National Formulary, and the Personal and Social Services Research Unit (PSSRU). We will calculate mean (SD) and median (IQR) costs for both study arms for each cost component and all components combined.

Cost-effectiveness will be measured in terms of the incremental cost per QALY gained. We will adapt a previously-developed decision analytic model which compared the cost-effectiveness of three strategies: Cytosponge™ screening with confirmatory endoscopy, endoscopy alone, and no screening, for 50 year-old men with GERD. The parameters for prevalence of BE, sensitivity and specificity of screening, uptake of the Cytosponge-TFF3 test, costs and utilities will be updated to reflect the BEST3 data. For these and all other parameters, including disease progression and management strategies, we will search the literature for updated evidence. We will extend the modelled population to also include women over 60 years, obtaining gender/age-specific parameters from BEST3 or searches of the literature where necessary. We will also undertake value-of-information (VoI) analyses, based on the notion that investing in further research on probabilities of events, HRQL and costs will reduce decision uncertainty about the cost-effectiveness of the Cytosponge-TFF3 test. This will include both the expected value of perfect information (EVPI) and the expected value of partial perfect information (EVPPI). The latter focusing on individual model parameters or groups of parameters.

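### GP and nurse visits are extracted only for the follow-up year, so consultation cost cannot be adjusted for its own baseline value: a modest loss of precision, not a bias

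*Protocol article*

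**What the plan says.** All references are to the protocol article.

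- **Status of the comparison** (Secondary objectives): "The main secondary objectives are to evaluate the cost and cost-effectiveness of the Cytosponge™-TFF3 test versus usual care". Table 2 and the Economic evaluation section both count primary-care follow-up among the cost components.
- **Baseline extract** (Aggregate data collection for BEST3 trial): "At this point demographic and medication data will be extracted from the GP database for every patient entered into the study". The baseline column of Table 4 holds sex, age, obesity, smoking and alcohol. For the preceding 12 months it adds acid-suppressant prescriptions, other prescriptions and reflux symptoms.
- **Follow-up extract** (same table): "Number of GP and practice nurse visits at home and at the practice" and "Number of endoscopy or GI referrals" appear in the follow-up column only. The section also says that "Full baseline data will also be extracted" at that time.
- **Costing window** (Economic evaluation, Primary endpoint): "Volume of resource use data will be collected from practice records up until 12 months after study entry". No pre-entry period is given.
- **Cost summary** (same section): "We will calculate mean (SD) and median (IQR) costs for both study arms for each cost component and all components combined".

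**The concern.** Past consultation is the natural covariate for later consultation. In a trial randomised largely by practice, it is also the natural guard against one arm happening to receive more high-attending practices. The baseline search already reads the same records over the right 12 months, but it does not count visits.

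The omission sits in the data specification, not in the analysis. A statistical or health-economic plan that is not shown could add clustering or covariates, but it could not adjust for a pre-entry visit count that the extract leaves out. The extract is also anonymised and aggregated by sex and 10-year age group, so the count could not be rebuilt from the trial dataset afterwards. At stake is the precision of the consultation-cost contrast within a main secondary objective.

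**Working it through.** **Does the plan supply a baseline visit count?** Table 4 has no visits in its baseline column. The sentence on re-extracting full baseline data sits beside that table and, read with it, repeats the baseline column. The costing window names no period before entry. So as written the count is not collected.

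**The plan's own figures.** The article states no sample size, ICC or precision for cost. Its ICC of 0.025 is for the primary endpoint. With the stated coefficient of variation of 0.2 and a cluster size of 55, it reproduces the stated inflation factor: 1 + ((1 + 0.2²) × 55 − 1) × 0.025 = 2.405, against 2.4. It says nothing about visits, so below it is only one of several assumed values.

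**Inputs from the article** (Pilot phase and 6-month milestone review): 11,816 patients in 100 cluster-randomised practices, so m = 11,816/100 ≈ 118 per practice. Allocation is 1:1, so about 50 practices per arm. A further 3840 patients are individually randomised.

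**Assumptions:** ICC for visits 0.01 to 0.10; practice-level correlation r between baseline-year and follow-up visits 0.5 to 0.8; equal practice sizes.

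**Cluster part.** In units of the patient-level standard deviation, the standard error (SE) of the arm difference is

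SE = √{2 × [ICC + (1 − ICC)/m] / 50}.

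With a practice-level baseline covariate, ICC in the first term becomes ICC × (1 − r²).

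Example at ICC 0.025: √{2 × [0.025 + 0.975/118]/50} = 0.0365. With r = 0.5 the first term is 0.01875 and the SE is 0.0329. With r = 0.8 it is 0.009 and the SE is 0.0263.

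| Assumed ICC | SE, no covariate | SE, r = 0.5 | SE, r = 0.8 | Fall in SE |
|---|---|---|---|---|
| 0.01 | 0.0271 | 0.0252 | 0.0219 | 7-19% |
| 0.025 | 0.0365 | 0.0329 | 0.0263 | 10-28% |
| 0.05 | 0.0482 | 0.0427 | 0.0323 | 11-33% |
| 0.10 | 0.0656 | 0.0575 | 0.0418 | 12-36% |

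**Individually randomised part.** Arms are compared within practices, so practice differences cancel and a practice-level covariate adds nothing. SE = √(4/3840) = 0.0323.

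**Whole trial.** By inverse variance at ICC 0.025, the individual part has 1/0.0323² ≈ 960 and the cluster part 1/0.0365² ≈ 752. The individual part therefore carries 960/1712 = 56% of the weight. The combined SE is 1/√1712 = 0.0242 without the covariate. It becomes 0.0230 at r = 0.5 (a fall of 4.7%) and 0.0204 at r = 0.8 (15.7%). The same calculation gives falls of 4.3-12.7% at ICC 0.01, 4.0-14.9% at 0.05 and 2.8-11.8% at 0.10. Over the assumed range, the overall gain is therefore about 3-16% in SE.

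**Bias.** Under 1:1 randomisation the expected practice imbalance is zero, with or without the covariate.

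**The case against.** A reader might infer that practice differences will be reported as if they were effects of offering the test. The documents do not support that. Practices are randomised 1:1, so these differences add variance, which a cluster-aware standard error covers. They would be mistaken for an arm effect only if the interval ignored clustering. The Economic evaluation section is silent on this: it describes a summary by arm and neither specifies nor rules out an adjusted, clustered contrast. That detail may properly sit in a plan that is not shown, so its absence is no finding.

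A reader might also infer that no adjustment for prior use is possible. That is too broad. Prior-year prescriptions and reflux symptoms are collected, and medication is itself a cost component in Table 2. A baseline count of GI referrals would add little, since Table 3 excludes "Recorded upper GI endoscopy in the previous 5 years as identified from the practice database". The test itself has no pre-entry counterpart. What remains is one covariate for one component of cost.

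The cluster share of participants, 11,816/15,656 = 75.5%, also overstates the exposure. The article values those patients as equivalent to 2924 of 6764 individually randomised ones, or 43%, for the primary endpoint. The weighting above points the same way for cost.

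The omission is also not irreversible: GP records persist, and a look-back could still be run at the 12-month extract. Finally, nothing in the article shows that the cost-effectiveness ratio depends on the between-arm visit-cost contrast.

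All of this stands and limits the point. It does not remove the core: a visit count left out of both the baseline column and the costing window cannot be used by any analysis plan.

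**Conclusion.** The point holds as a minor one. As specified, the consultation component of the main secondary cost comparison cannot be adjusted for its own baseline value. The loss is in precision and in protection against chance practice imbalance; validity is not affected.

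The size is illustrative. It rests on assumed ICCs of 0.01 to 0.10 and assumed practice-level correlations of 0.5 to 0.8, neither of which the article gives. On those assumptions the standard error falls by about 7-36% in the cluster-randomised part and about 3-16% overall. Both figures concern consultation cost, not total cost.

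**What to change.** 1. Add to the baseline column of Table 4 the number of GP and practice nurse visits in the 12 months before study entry. For practices whose baseline extract is already done, collect it when baseline data are pulled again at 12 months. A prior-year count of GI referrals is optional and of little value.
2. State in the economic analysis plan that the between-arm difference in consultation cost is estimated with adjustment for that count, at practice or age-sex stratum level because the data are aggregated, and with an interval that allows for clustering in the cluster-randomised part.

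**Cost:** one more field with a look-back date in an existing search, and a little more analysis work. No patient contact is needed, and neither the sample size nor the primary analysis changes.

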#### Long term follow-up

When suitable anonymisation models become available, long term cancer registration and mortality data will be obtained from NHS Digital and the NHS Health and Social Care Information Centre (HSCIC) or equivalent. Data sent from HSCIC to QMUL will always be anonymised and aggregated by practice. Individually-consented participants in the trial may have their longer-term heath status followed up via data held by NHS Digital, HSCIC or its successor, the Office of National Statistics, Public Health England and other national databases.

### BEST3 intervention: Cytosponge™-TFF3 test

#### Patient invitation to BEST3 intervention

All participants in the intervention arm, who have not opted out of the study, will receive a second letter from their GP team inviting them to have the Cytosponge™-TFF3 test. This communication will include a standalone Cytosponge™ information leaflet (Additional file 1: Figure S1). This leaflet was developed based on findings from a qualitative study on the acceptability of the Cytosponge™ test [19] followed by several rounds of review by patient and public involvement (PPI) representatives. Once a participant has expressed interest by returning a reply slip or telephone call, the participant will receive a telephone call to further assess eligibility based on a short questionnaire. If eligible, an appointment will be arranged. The participant will then be sent a Cytosponge™ patient information sheet, consent form and appointment confirmation.

#### Cytosponge™ clinic procedure

Cytosponge™ clinics for participants from several practices will be held by either a CRN or local practice nurse with appropriate medical cover in place. Participants will be asked to refrain from eating and drinking for 4 h. Once consent has been obtained, the nurse will complete a questionnaire on demographic and clinical information and the previously validated GERD Impact Scale (GIS) with the participants [20] using case report forms (CRFs) in the BEST3 Database.

Patients will be asked to swallow the capsule with water. The capsule reaches the stomach while remaining attached to the string which is held onto by the patient or nurse (and which is affixed to a card preventing inadvertent swallowing of the entire string). In the stomach the capsule is left for up to 5 min where it dissolves allowing the sponge to expand to its full size. It is then withdrawn by the research nurse using the string, and as it does so collects cells from the lining of the oesophagus. The retrieved sphere is placed in preservative liquid. Linked anonymised samples will be sent directly from the practice to the pathology laboratory to be processed and analysed for TFF3 and H&E.

If a patient fails to swallow the capsule, they will be asked to try again. In the event of a Cytosponge™ detachment or an obvious bleed the research nurse will immediately inform the GP as the patient falls under their duty of care for medical assessment. Following medical assessment, the GP’s normal emergency procedures will be followed. The research nurse will telephone all participants who received the Cytoponge™ at 7 days post-procedure to assess safety and report adverse events.

